12. Triplicate measurements of 12-lead ECGs (recommended to perform 3 ECGs within 5 minutes) will be recorded during screening, pre-dose on Day 1 of each Cycle, at end of treatment, and post-dose on the indicated study days (refer to [Table 1-6](#)) (pre- and post-dose procedures in BID cohort will only be required for the first dose during the day) and read by the central laboratory. The time for post-dose ECG is recommended to be as close as possible to the PK sampling time unless it's too difficult for clinical practice.
13. [REDACTED]  
[REDACTED]  
[REDACTED]
14. Each subject will receive an oral dose of D-1553 (once daily or BID) at RP2D on an empty stomach (no food and drink, except for water, for at least 0.5 hours before and after dosing) from Day 1 to Day 21. Each 21-day period will be considered as 1 treatment cycle. Subjects may continue with once daily or BID administration of D-1553 until disease progression, unacceptable treatment related toxicity, withdrawal of consent or discontinuation from the study for other reasons, whichever occurs first. D-1553 will be dispensed on Day 1 of each cycle together with the instruction of taking the drug at home and the diary for recording of dose taken.

15. At selected sites, up to a total of 30 phase 2 subjects will also be consented to have intensive PK and ECG data collected (Table 1-6). Sparse PK sampling will be collected in the other subjects (Table 1-6).
16. Radiologic imaging will be used for tumor assessment. A CT scan (with or without contrast) of the chest, abdomen and pelvis will be performed to assess metastatic disease. A bone scan will be performed in the event of clinical symptoms of bone metastases. A baseline brain MRI (with or without contrast; CT is acceptable if MRI is contradicted), should be performed for subjects with a history of or suspected to have CNS metastases. For subjects with no CNS metastases at baseline, it is not necessary to repeat brain MRI unless CNS involvement is suspected during the study. Screening scans can be performed within 6 weeks prior to Day 1 of treatment cycle 1. Tumor assessment will be performed at screening and the completion of every 2 treatment cycles for the first 8 treatment cycles, thereafter the completion of every 3 treatment cycles until disease progression, start of new anticancer treatment, death, withdrawal of consent, or until end of study. There is a  $\pm 7$ -day window for each tumor assessment.
17. [REDACTED]

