[REDACTED]  
[REDACTED]  
[REDACTED]

19. [REDACTED]  
[REDACTED]  
[REDACTED]  
[REDACTED] Subjects will receive cetuximab: 400 mg/m^2 initial dose (120-minute IV infusion on Cycle 1 Day 1), then 250 mg/m^2 (60-minute IV infusion) once weekly. Thereafter, each 21-day cycle will be considered as 1 treatment cycle. D-1553 and cetuximab may continue until disease progression, unacceptable treatment related toxicity, withdrawal of consent or discontinuation from study for other reasons, whichever occurs first.
20. At selected sites, up to a total of 30 phase 2 subjects will also be consented to have intensive PK and ECG data collected ([Table 1-6](#)). Sparse PK sampling will be collected in the other subjects ([Table 1-6](#)).
21. Radiologic imaging will be used for tumor assessment. A CT scan (with or without contrast) of the chest, abdomen and pelvis will be performed to assess metastatic disease. A bone scan will be performed in the event of clinical symptoms of bone metastases. A baseline brain MRI (with or without contrast; CT is acceptable if MRI is contradicted), should be performed for subjects with a history of or suspected to have CNS metastases. For subjects with no CNS metastases at baseline, it is not necessary to repeat brain MRI unless CNS involvement is suspected during the study. Screening scans can be performed within 6 weeks prior to Day 1 of treatment cycle 1. Tumor assessment will be performed at screening and at the completion of every 2 treatment cycles for the first 8 treatment cycles, thereafter at the completion of every 3 treatment cycles until disease progression, start of new anticancer treatment, death, withdrawal of consent, or until end of study. There is a  $\pm 7$ -day window for each tumor assessment.
22. [REDACTED]  
[REDACTED]
23. These procedures can be done on Day -1 or Day 1 but have to be completed prior to first dose of study intervention. They are intended for checking the subject status before the first dose, not for eligibility. A subject's eligibility should be determined during the screening period. Laboratory tests performed in the screening period within 7 days of Day 1 do not need to be repeated on Day -1 or Day 1 unless clinically indicated.
24. These visits need to be completed within 7 days of the last dose of study intervention:
- Subjects who stop treatment due to disease progression at the visit time do not need to repeat the imaging examination;

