**Table 4-3 Simon 2-stage design futility criteria for**

| The alternative vs null objective response rate rates (P1 vs P0) | Futility stage 1 | Futility stage 2 | Applies to |
|------------------------------------------------------------------|------------------|------------------|------------|
|                                                                  |                  |                  |            |
|                                                                  |                  |                  |            |
|                                                                  |                  |                  |            |

Arms B are for single agent D-1553 treatment and Arms F are for combination treatments, as follows:

- 
- Arm B: solid tumors other than NSCLC treated with D-1553 single agent at RP2D;
- 
- 
- 
- 
- Arm F: CRC, D-1553 in combination with cetuximab

Upon completion of Phase 1a (single agent dose escalation), Phase 2 Arms B may be started, while Phase 2 Arms F may be started once Phase 1b (dose combination) is completed. The sequence of enrollment to each group or arm will be communicated to investigational sites by study team. Each arm will enroll approximately 30 subjects for evaluation of safety and efficacy in subjects with KRASG12C bearing solid tumors. If 1 or more arms demonstrate significant antitumor activity that

Each subject will receive an oral dose of D-1553 at RP2D. Each 21- or 28-day period will be considered as 1 treatment cycle. Subjects may continue with daily administration of D-1553 until disease progression, unacceptable treatment-related toxicity, withdrawal of consent or discontinuation from the study for other reasons, whichever occurs first. In the combination arms, D-1553 may be continued at the same dose level after the combination regimen is completed, if the investigator considers it is in the best interest of the subject, after consulting with the sponsor's medical representative. [REDACTED]

Subjects who do not have disease progression on study will be followed for tumor assessment, approximately every 12 weeks ( $\pm 2$  weeks), until disease progression, death, lost to follow-up, start of another anticancer therapy, or other reasons that a follow-up is not possible. Subjects will be followed for survival status monthly ( $\pm 2$  weeks), until death, lost to follow-up or other reasons that a follow-up is not possible. The follow-up can be done via telephone call.

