### 6.2.7 Dose Interruptions/Delay/Reductions

Dose reductions of D-1553 may be required based on the worst toxicity experienced. In the event that a study drug related Grade 3 or higher toxicity occurs, defined in the NCI CTCAE v5.0, administration of D-1553 should be held until the drug related toxicity has resolved to grade 1 or baseline. Upon resolution of the toxicity or return to baseline, the subject should resume their current assigned dose of D-1553 or at the next lower dose level after discussion with sponsor. The following guidance can be used:

- After Cycle 1 Day 1, a treatment delay or dose interruption of more than one treatment cycle (21 or 28 days after the current cycle) will result in treatment discontinuation unless the subject is receiving clinical benefit as judged by the investigator and after discussion with the sponsor.
- Doses delayed or missed will not be made up (i.e., cycles will not be prolonged beyond the 21st or 28th calendar day in order to make up any missed doses).
- If a treatment interruption continues beyond Day 21 or Day 28 of the current cycle, then the day when treatment is resumed will be counted as Day 1 of the next cycle.

For subjects who experience a recurrent study drug related Grade 3 or higher toxicity, a discussion between the sponsor and investigator will occur to determine whether the subject should continue in the study. For any subject experiencing a Grade 3-4 toxicity, treatment should be resumed at next lower dose level after toxicity resolves to Grade 1 or baseline. A subject who experiences the same serious adverse event (SAE) of the same NCI CTCAE toxicity grade or higher related to D-1553 must discontinue the treatment immediately. Any subject with liver function test abnormalities meeting Hy's Law\* criteria [REDACTED]

[REDACTED] must be permanently discontinued,  
[REDACTED]  
[REDACTED]  
[REDACTED]

\* Hy's Law: ALT or AST  $\geq 3 \times$  ULN, TBIL  $\geq 2 \times$  ULN in the absence of cholestasis (serum alkaline phosphatase [ALP]  $> 2 \times$  ULN), and there are no other reasons to explain the combined elevation of aminotransferase and TBIL.

[REDACTED]

In combination cohorts, the combination drugs (other than D-1553) may have dose interruption, delay, reduction or other modifications according to their prescribing information.

[REDACTED]

[REDACTED]

\_\_\_\_\_

\_\_\_\_\_

[REDACTED]

\_\_\_\_\_

\_\_\_\_\_

[illegible]

[illegible]

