## **7 STUDY PROCEDURES**

Study procedures and their time points are summarized in the Schedule of Assessments (see Table 1-1 through Table 1-3). Refer to the investigational product, laboratory and site imaging manuals for detailed collection and handling procedures.

Adherence to the study design requirements, including those specified in the Schedule of Assessments, is essential and required for study conduct.

A signed and dated IRB/IEC approved ICF must be obtained prior to performing any study specific procedures, including discontinuing standard therapy for observing study specific washout periods.

Subjects will be seen in the clinic for study evaluations. During all visits' invasive procedures like blood draws or biopsies should be completed after ECGs and vital signs.

Blood samples for biomarker and PK assessments should be drawn from a peripheral vein and not from a central venous catheter. The study specific lab manual will provide additional detail on lab sampling and handling requirements.

Furthermore, start of a treatment can be delayed for administrative/logistical reasons for up to 7 days to allow for appropriate scheduling after discussion with and final approval by sponsor.

Any missed visits, tests not done, or examinations that are not conducted must be reported as such on the eCRFs. Subsequent study visits should resume on the original schedule. Missed assessments at prior visits should not be duplicated at subsequent visits. Every effort should be taken to collect all biomarker and PK samples as described in the schedule of assessments.

Additional procedures deemed necessary as part of standard of care or as required by local laws and regulations may be performed at the Investigator's discretion.

At selected sites, up to a total of 30 phase 2 subjects will also be consented to have intensive PK and ECG data collected according to Table 1-6.

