#### **7.2.7 Phase 2 - Day 1 of Treatment Cycle $\geq$ 2**

- Physical examination
- ECOG performance status
- Vital signs
- Laboratory assessments (including hematology, blood chemistry, urinalysis, coagulation etc.)
- Pregnancy test (serum or urine) is required for female subjects with childbearing potential in odd-numbered cycles.
- 12-lead ECG
- [REDACTED]
- LVEF measurement with Echocardiogram (only for Arm [REDACTED] F)
- [REDACTED]
- PK collection
- [REDACTED]

- Study intervention
- Dispense study drug and instructions for dosing at home
- Dispense diary card
- AE assessment
- Futility assessment (per arm according to Simon 2-stage design when stage 1 is completed for the respective arm)
- Concomitant medication review
- Tumor assessment at the completion of treatment cycle 2 (assessment performed every 2 treatment cycles for the first 8 treatment cycles and every 3 treatment cycles thereafter until disease progression, start of new anticancer treatment, death, withdrawal of consent, or until end of study.)

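### On-treatment tumor scans are counted in cycles, and a dose hold that overruns the cycle restarts the count, so scan dates drift with toxicity and blur PFS and DOR

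*Protocol*

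**What the plan says.** **Scan schedule.** For Arm B, Table 1-3 (footnote 16) sets scans at screening and "the completion of every 2 treatment cycles for the first 8 treatment cycles, thereafter the completion of every 3 treatment cycles". For Arm F, Table 1-4 (footnote 21) sets them "at the completion of every 2 treatment cycles for the first 8 treatment cycles, thereafter at the completion of every 3 treatment cycles". Section 7.2.7 repeats the count: "assessment performed every 2 treatment cycles for the first 8 treatment cycles and every 3 treatment cycles thereafter until disease progression". Tables 1-1 and 1-2 and Section 7.1.7 do the same for Phase 1. Each table allows ±7 days around a scan, and none converts the count to weeks from Cycle 1 Day 1.

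**Cycle length.** Table 1-3 says "Each 21-day period will be considered as 1 treatment cycle". Section 4.1.3 says for Phase 2 as a whole "Each 21- or 28-day period will be considered as 1 treatment cycle". Arms B and F both use 21 days.

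**Cycle count after a hold.** Section 6.2.7 distinguishes two cases. For a hold that ends inside the cycle, "Doses delayed or missed will not be made up" and the cycle is not prolonged. For a hold that runs past the last day of the cycle, "then the day when treatment is resumed will be counted as Day 1 of the next cycle". A delay of more than one cycle ends treatment, unless the investigator judges that the subject benefits and the sponsor has been consulted.

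**Missed visits.** After requiring that missed visits and tests be reported, Section 7 adds: "Subsequent study visits should resume on the original schedule".

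**Assessments that do have a calendar count.** LVEF in Table 1-4 (footnote 15) is due every 4 cycles, glossed as 12 weeks, from Cycle 1 Day 1. Scans after treatment in subjects without progression are due about every 12 weeks (Table 1-3 footnote 21, Table 1-4 footnote 26).

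**The concern.** Progression and response are recorded at the scan that shows them, so PFS and DOR depend on when scans are done. If scan dates follow a cycle count that restarts after a long hold, they depend on toxicity and, for the longest holds, on the investigator's view of benefit. Two subjects with the same tumor course can then have different recorded PFS because one had a hold.

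A scan taken late under this rule is not a deviation, since the window is attached to the cycle-defined date. The analysis plan cannot restore a scan that was not taken.

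A site also has no explicit answer to the practical question of whether, after a cycle has restarted, the next scan follows the calendar or the new count.

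**Working it through.** The protocol states no figure on this point to reproduce, so the check is the calendar arithmetic followed by its effect on recorded PFS and DOR.

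**1. Scan dates without holds (21-day cycles).**
- 2 cycles = 2 × 21 = 42 days = 6 weeks; 3 cycles = 63 days = 9 weeks.
- Scans at the end of cycles 2, 4, 6, 8, 11, 14 fall on days 42, 84, 126, 168, 231, 294, which are weeks 6, 12, 18, 24, 33, 42.
- Consistency check: 4 × 21 = 84 days = 12 weeks, as the LVEF footnote states.
- For 28-day cycles the intervals are 8 and 12 weeks.

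**2. One hold that overruns Day 21 by h days.** The interval becomes (42 + h)/7 or (63 + h)/7 weeks.

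| h (days) | 6-week interval becomes | 9-week interval becomes |
|---|---|---|
| 7 | 7 weeks | 10 weeks |
| 14 | 8 weeks | 11 weeks |
| 21 | 9 weeks | 12 weeks |

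All later scans move by h. With h above 7 the scan lies outside ±7 days of its original date but still complies. A hold ending inside the cycle gives h = 0 and moves nothing.

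**3. Mean recorded PFS.** Simulation with exponential true PFS and progression dated at the next scan. These assumptions are not in the protocol: true median 4 or 6 months, and 10–30% of cycles followed by a 1–3 week overrun. Over four cycles those rates mean that 1 − 0.9⁴ = 34% to 1 − 0.7⁴ = 76% of subjects have at least one overrun.
- Mean recorded PFS rises by about 0.06 to 0.2 months (about 2 to 6 days) against a fixed calendar grid.
- Under a different assumption, with one or two overruns of 14 or 21 days in cycles 1–4, the rise is 0.2 to 2.3 days if 20–40% of subjects are affected and about 1 to 6 days if all are.

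**4. Median recorded PFS.** The median falls on a scan date, so its shift depends on where the true median lies on the grid. Suppose every subject has one 21-day overrun in cycles 1–4. The scans after cycles 6 and 8 then move from days 126 and 168 to days 147 and 189. One month is 30.44 days.
- True median 4 months = day 122. It is recorded at day 126 (4.14 months) without holds and day 147 (4.83 months) with them: +21 days.
- True median 6 months = day 183. It is recorded at day 231 (7.59 months) without holds and day 189 (6.21 months) with them: −42 days.

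The simulation in step 3 shows the same pattern. At a true 4 months the recorded median goes from 4.14 to about 4.65–4.88 months. At a true 6 months with 30% of cycles overrunning it goes from 7.59 to about 6.84.

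**5. DOR.** Assumed: true response at day 20, true progression spread evenly over days 60–300, one 21-day overrun.
- Overrun in cycle 1 or 2, before the first scan: onset is recorded 21 days later, progression only slightly later on average, and mean DOR is about 20 days shorter.
- Overrun in cycles 3–6, after response was seen: mean DOR is about 1 to 3 days longer.

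**6. With scans fixed to calendar weeks,** the shift due to holds is 0 days by construction.

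**The case against.** The case for leaving the text alone has several sound parts.

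- **Limits already in place.** Only holds that overrun the cycle move scans. A hold beyond one cycle normally ends treatment, the end-of-treatment scan is repeated if the last one is more than 4 weeks old, and later scans follow the calendar. This stands and limits the size of the effect.
- **Small average effect on secondary endpoints.** ORR is primary, and the analyses stated for PFS and DOR are descriptive. The mean shift of 2 to 6 days is inside the ±7-day window and rests on assumed hold rates. This also stands.

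A reader might infer more than the documents support:

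- **That the rule lengthens PFS and DOR in general.** Only mean PFS rises consistently. The median PFS that the protocol will report can fall, and DOR shortens when the hold precedes the first response scan.
- **That Section 7 contradicts Section 6.2.7.** Its sentence follows one on missed visits and tests and mentions neither holds nor scans. Both rules can be followed together. The gap is that the schedule meant there is not defined for imaging after a restart.
- **That Arm F is distorted more than Arm B.** The protocol gives no hold rates by arm. Section 6.2.7 concerns D-1553 and refers combination drugs to their prescribing information, and no text says that omitting cetuximab restarts a cycle. Both arms use 21-day cycles, so the 6- versus 8-week difference is not between them.
- **That confirmation of response drifts too.** It is recommended at an interval of at least 4 weeks, not by cycle count.

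None of this supplies a calendar anchor for the on-treatment scans.

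**Conclusion.** The point holds as a cheap improvement, not as a serious flaw. Followed as written, Section 6.2.7 and the cycle-counted scan schedule make scan dates depend on toxicity. One overrun of up to 21 days turns a 6-week interval into as much as 9 weeks, or a 9-week interval into 12, without a deviation. That part is arithmetic from the protocol's own rules.

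The effect on the endpoints rests on assumed PFS distributions and hold rates. It is a distortion rather than a bias in one direction: mean PFS slightly up, median PFS either way, DOR down or up according to whether the hold comes before or after first response. ORR depends little on it, because a hold mainly changes when a response is seen. The case for acting is that the drift is avoidable by wording and cannot be repaired at analysis.

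**What to change.** - **Tables 1-1 to 1-4 (tumor assessment footnotes) and Sections 7.1.7 and 7.2.7:** state tumor assessments in calendar weeks from Cycle 1 Day 1, irrespective of dose holds. For 21-day regimens: weeks 6, 12, 18, 24, then every 9 weeks, ±7 days. For 28-day regimens: weeks 8, 16, 24, 32, then every 12 weeks, ±7 days. These are the existing intervals converted to weeks.
- **Section 6.2.7:** add that restarting the cycle count does not move tumor assessments.
- **Section 7:** say that, for imaging, the original schedule means these calendar dates.

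The dose-hold rules need no change for this.

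The cost is wording, plus some scans that no longer fall on a Day 1 visit. Subjects without holds have the same number of scans. Those with holds may have slightly more scans per cycle received.

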**C Confidential**

[illegible]

\_\_\_\_\_

[illegible]

**C Confidential**

[illegible]

[https://www.accessdata.fda.gov/drugsatfda\\_docs/label/2019/125084s2731b1.pdf](https://www.accessdata.fda.gov/drugsatfda_docs/label/2019/125084s2731b1.pdf)

Cetuximab will be administered IV weekly on Days 1, 8, and 15( $\pm 3$  days) of every 21-day cycle at the study site according to institutional standards. The initial cetuximab dose (Cycle1 Day 1) is 400 mg/m^2 administered as a 120-minute IV infusion followed thereafter by a 250 mg/m^2 dose

administered as a 60-minute IV infusion. The infusion rate should be consistent with the local label but should not exceed 10 mg/min. Close monitoring is required during the infusion and for at least 1 hour after the end of the infusion. If an infusion reaction occurs while cetuximab is being administered, the infusion should be stopped immediately, and the patients should be closely monitored and treated in line with institutional standards. Any rechallenge with cetuximab following an infusion reaction should be first discussed with the Sponsor.

Premedications for routine cetuximab infusions may be used in accordance with the label and with the national and/or institutional standards, but preferably be based on a combination of an H1 antagonist (e.g., diphenhydramine) and dexamethasone (10 mg IV). Premedications should be administered approximately 30 minutes prior to cetuximab infusion. Following cetuximab label instructions, medications such as corticosteroids and antihistamines may be administered at the discretion of the Investigator to treat an existing infusion reaction, or as premedication for a patient who has previously experienced an infusion reaction.

Doses of cetuximab that are omitted for AEs or any other reason should not be made up.

## 6.5.2 Dose Modification

Recommended dose modifications for cetuximab based on the occurrence of cetuximab treatment-related AEs are summarized.

| Worst toxicity
CTCAE, Grade                | Dose Modification for Cetuximab During a Cycle of Therapy                                                                                                                                                                                                                                                                                                                                                                                 |
|-----------------------------------------------|-------------------------------------------------------------------------------------------------------------------------------------------------------------------------------------------------------------------------------------------------------------------------------------------------------------------------------------------------------------------------------------------------------------------------------------------|
| Infusion Reaction                      | If an infusion reaction occurs while cetuximab is being infused, the infusion should be stopped immediately and the patient should be evaluated.                                                                                                                                                                                                                                                                                          |
| Grade 1 or 2                                  | Restart and complete the disrupted infusion at the discretion of the Investigator. The infusion must be restarted at a reduced rate. Additional pre-medications such as antihistamines or low-dose systemic corticosteroids may be administered when the infusion is restarted per institutional standards.
All subsequent infusions must also be administered at the reduced rate.                                                    |
| Grade 3 or 4                                  | Permanently discontinue cetuximab                                                                                                                                                                                                                                                                                                                                                                                                         |
| Rash                                   |                                                                                                                                                                                                                                                                                                                                                                                                                                           |
| Grade 1 or 2                                  | Maintain dose level; consider initiating appropriate therapy (such as antihistamines, topical corticosteroids, and low-dose systemic corticosteroids)                                                                                                                                                                                                                                                                                     |
| Grade 3, despite therapy                      | Omit dose until resolved to ≤ Grade 2, then: 
 
• If resolved in ≤ 7 days (or ≤ 14 days for acneiform rash), then maintain dose level
 
• If not resolved in ≤ 7 days despite appropriate skin toxicity therapy (or ≤ 14 days for acneiform rash), then permanently discontinue cetuximab
 
                                                                                           |
| Grade 3 recurrent                             | Omit dose until resolved to ≤ Grade 2, then: 
 
• If resolved in ≤ 7 days (or ≤ 14 days for acneiform rash), then decrease 1 dose level
 
• If not resolved in ≤ 7 days despite appropriate skin toxicity therapy (or ≤ 14 days for acneiform rash), then permanently discontinue cetuximab
 
• Permanently discontinue cetuximab after 3rd recurrence (upon 4th occurrence)
 
 |
| Grade 4, despite skin toxicity therapy | Permanently discontinue cetuximab                                                                                                                                                                                                                                                                                                                                                                                                         |

